## Abstract

**Background:**

Comorbidity is prevalent among people with multiple sclerosis (pwMS) and may contribute to disease progression. Physical exercise (PE) reduces symptoms in pwMS and also benefits comorbidities. Digital (e)-based PE has been proposed as a tool to support the integration of PE.

**Aims:**

To describe a protocol for a randomized controlled trial (RCT) based on a structured approach and the results from a controlled feasibility study of an e-based PE intervention in pwMS with and without comorbidities.

**Method:**

In a RCT following a feasibility study (n=50), patients will be randomly assigned in a 1:1 ratio to receive either usual care (n=150) or usual care plus an e-based PE program at home (n=150). The exercise program consists of resistance training with resistance bands targeting the lower extremities. The sessions will enable participants to engage in group exercises from their homes, supervised online by physiotherapists, two 60-minute sessions per week for 6 months (24 weeks and 48 sessions). The primary endpoint is change of walking capacity using the 6-minutes’ walk test. Secondary endpoints include “no evidence of disease activity” (NEDA)-3 scale, measures of quality of life and fatigue as well as levels of neurofilament light chain in blood and cerebrospinal fluid.

Results of the feasibility study: Fifty individuals were eligible and randomized to an intervention group (n = 23) or to a usual care control group (n = 27). A total of 24 sessions were conducted for three months in groups of 6, supervised by the physiotherapist. In the intervention group, two pwMS did not begin the PE program due to occupational constraints with a resulting recruitment rate of 91.3% (21/23). Of the remaining 21 individuals, 16 (76.2%) completed the follow-up assessments with a mean attendance of 15.2 (range 6-22) sessions per participant, corresponding to a 63% adherence rate. No intervention‐related adverse events were reported.

**Conclusion:**

This protocol describes a prospective RCT study and the supporting feasibility data of an e-based PE performed at home. The effects of e-based PE performed at home will be evaluated, offering a significant contribution to the field of digital healthcare solutions and MS.

**Clinical Trial Registration:**

https://clinicaltrials.gov/, identifier NCT06298201.

## Introduction

1

Multiple sclerosis (MS) is a potentially disabling inflammatory demyelinating disease of the central nervous system (CNS). It manifests as a consequence of immune attacks on myelin and nerve fibers which leads to neuronal damage (neurodegeneration) and subsequently to the clinical accumulation of neurological disability (1–5).

Over the last two decades, the age-specific prevalence of people with MS (pwMS) has increased substantially (6–8), and aging will expectedly amplify the risk of comorbidities and conversion into a progressive disease course (9). Comorbidity refers to the total burden of any additional entity other than the specific index disease (10, 11) Physical inactivity is a major risk factor for the development of comorbidity in pwMS (10). Emerging evidence underscores the high prevalence of comorbidity in pwMS, evident even at the time of MS diagnosis (10, 12). This is of importance as comorbidities can lead to delayed MS diagnosis, accelerated disease progression, and diminished efficacy and safety of MS treatments, subsequently increasing mortality (10, 13–15). Cardiovascular disorders comorbidities and related risk factors (RF) including type 2 diabetes mellitus (T2DM), obesity, hyperlipidemia and hypertension are prevalent among pwMS (12, 16).

Physical exercise (PE) is advocated as an effective treatment for at least 26 chronic diseases, including MS (17–19). In pwMS, PE positively modulate peripheral inflammatory markers such as TNF-alpha, INF-gamma, IL-4, IL-10, etc. (20–22), while also reducing the relapse rate (23). PE improves muscle strength and cardiorespiratory fitness (24–26), as well as walking speed, endurance (27–30), and balance in MS patients (31). Furthermore, PE can induce reductions in fatigue (32–40) and symptoms of depression, and improvements in cognitive dysfunction as well as quality of life in MS patients (35, 41–47). In pwMS, walking impairments are highly prevalent and up to 68% of the patients experience some degree of ambulatory dysfunction (48). Since walking is a cornerstone in the ability to perform activities of daily living, and to retain working capacity (49), walking impairment also impact quality of life (50). The 6-Minute Walk Test (6MWT) is considered the gold standard (51), and able to predict habitual walking in pwMS (52).

Despite the benefits of PE for MS patients, a significant proportion drop out or fail to maintain an active lifestyle post-rehabilitation (53, 54). This trend is a serious challenge for integrating and sustaining PE in the daily lives of pwMS. Consequently, solutions that can support pwMS in sustaining a physically active lifestyle are warranted. A promising category of potential solutions covers eHealth devices and digital healthcare tools (55–59). The effectiveness of e-based MS rehabilitation, including telerehabilitation, has shown promising results in improving fitness, gait, balance, and upper limb function, often equaling or exceeding traditional treatment (60–64). Excluding pwMS from clinical trials based on the presence of comorbidity is common, which consequently leads to limited reports about the effect of comorbidities on outcomes of rehabilitation trials (65). Further research is required to investigate e-based PE’s effectiveness and long-term impact on managing pwMS with comorbidities. Significant knowledge gaps exist on the effect of PE on pwMS and comorbidities. The adaptation of exercise to comorbidity evidently adds challenges and complexity as to the application and integration of behavior change techniques, which may be applied to the exercise plan. Furthermore, most existing studies have excluded pwMS that had comorbidities at baseline (66). Accordingly, guidance and guidelines are not yet available for pwMS with comorbidity.

The aim of this randomized clinical trial (RCT) is to investigate if e-based PE, in addition to usual care, will be more effective than usual care alone in improving health outcomes for pwMS with and without comorbidities. Because the intervention focuses on progressive resistance training of the lower extremities, the 6-Minute Walk Test (6MWT) was chosen as the primary endpoint, reflecting expected improvements in walking endurance and functional mobility. Secondary endpoints capture disease activity and broader health impact, including NEDA-3 (relapses, EDSS progression, MRI activity), as well as measures of cardiorespiratory fitness (Ekblom–Bak test), accelerometer-measured activity, quality of life, fatigue, mood, sleep, pain, and biomarkers such as levels of neurofilament light chain (NfL).We hypothesize that PE significantly reduces disability, increasing walking capacity as the primary outcome for pwMS and comorbidity.

## Methods

2

### Study design

2.1

The schematic overview of the COMPACT workflow is illustrated in **Figure 1**. This protocol delineates a RCT with prospective longitudinal data collection in pwMS with or without comorbidity. To enhance the feasibility of the main study, a feasibility study was conducted, and we report the results in this article. The study is designed according to the SPIRIT statement for the RCT and the CONSORT pilot and feasibility extension for the feasibility study (67).

**Figure 1 f1:**
[figure not shown]
Flowchart of the randomized controlled trial design for evaluating the effects of a 6-month e-based supervised physical exercise intervention compared to usual care of patients with multiple sclerosis and comorbid conditions. The process outlines the stages from enrollment and baseline assessment until the 24-month follow-up. (*Month 3 assessments are limited to physical performance and self-reported measures. Neurological examinations, cognitive assessments, biospecimen collection, and MRI imaging are not conducted at this timepoint due to protocol constraints and participant burden considerations.).

### Participants

2.2

The study will include pwMS with comorbidity (n=150) (one or more comorbidities e.g. multimorbidity) or without comorbidity (n=150). The study population will be established based on the following inclusion criteria: 1) confirmed MS diagnosis in accordance with the international McDonald Criteria for MS 2017. [3], 2) Expanded Disability Status Scale (EDSS) assessment score of less than 7.0 at baseline (68), 3) adults aged 18 years or above.

Individuals will be excluded if they have 1) current drug or alcohol abuse, 2) steroid treatment in the past month, 3) pregnancy, 4) recent trauma, active systemic infections, cancer, other chronic conditions that preclude physical exercise e.g. Parkinson’s disease or have no access/ability to use e-based solutions.

### Recruitment procedure

2.3

Patients will be recruited from the Departments of Neurology, MS-Clinics in the Region Zealand, Denmark in collaboration with the Innovation and Research Centre for Multimorbidity at Slagelse Hospital and Department of Physiotherapy and Occupational Therapy, Slagelse. Other MS-clinics in Denmark will be requested to refer pwMS with or without comorbidity during the 2-year time period from September 1st, 2025, until May 31st, 2027. An introductory letter will be sent to the clinics, followed by further information.

### Comorbid conditions

2.4

At the study onset comorbidity data, including diagnosis dates, characteristics, and treatments, will be extracted from patients’ medical records, and supplemented by patient interviews as needed (69, 70). In addition, each comorbidity is categorized using the International Statistical Classification of Diseases and Related Health Problem (ICD-10) System (71). For analytical purposes, comorbidity will be characterized in several ways: (1) presence versus absence of any comorbidity, (2) number of comorbid conditions (none, single comorbidity or multimorbidity defined as ≥2 comorbid conditions), and (3) type of comorbidity. Where sample size allows, exploratory subgroup analyses will be performed according to the number and category of comorbid conditions. Patients will be grouped based on the presence and type of comorbid conditions which will be clustered into six categories being cardiovascular disorders and related RF, autoimmune diseases, mental and behavioral disorders, diseases of the respiratory system, diseases of the skin and diseases of the musculoskeletal system.

### Medical history and clinical examination

2.5

Clinical data including age, sex, ethnicity, height, weight, and lifestyle factors (e.g., tobacco and alcohol use, drug abuse history) will be recorded. Disease characteristics such as onset, current symptoms, relapse history, comorbidities, and treatments will be determined through clinical examination, interviews, and review of medical records. Disability progression will be monitored through changes in neurological status, which will be assessed with the EDSS (68), following Neurostatus definitions (72), and visual system evaluation will be conducted via best-corrected high-contrast visual acuity testing (73). Details about the initiation and cessation of disease-modifying therapies (DMT) will be recorded.

### Blinding and randomization procedure

2.6

Patients will be randomized in a 1:1 ratio into groups receiving either usual care or usual care plus a 6-month e-based PE program, using random blocks of 4 or 6 and stratified into two groups with comorbidity and without comorbidity. Randomisation will be made blindly based on ID assigned to each patient and be stratified by comorbidity status (presence versus absence of ≥1 comorbid condition) to ensure balanced allocation across study groups. Furthermore, the patients will be stratified by age, sex, and degree of disability (EDSS) in REDCap (74). Due to the nature of the intervention, it is not feasible to blind participants or physiotherapists delivering the program. Nonetheless, to preserve the integrity of the trial, outcome assessors (researchers) will remain blinded to the allocation of treatments as well as the interpretation of the data throughout the study **Table 1**.

**Table 1 T1:** Detailed overview of e-based exercise therapy intervention components.

Item No.	Item category	Description
1	WHAT: Materials	E-Based exercise therapy materials: elastic bands, chair, mat/blanket, camera-equipped device (computer/tablet), 65” widescreen with computer.
2	WHO: Provider	A licensed physiotherapist delivers the program.
3	HOW: Delivery	Exercises delivered in virtual groups (6–8 participants) using a wide screen and handouts.
4	HOW: Supervised/Unsupervised	Exercises are virtually supervised.
5	HOW: Measure Adherence	Attendance recorded by the physiotherapist post each session; exercise progression logged in patient diaries.
6	HOW: Motivation Strategies	Potential strategies include SMS or phone call reminders.
7	HOW: Rules for Progression	Progression guided by by Dalgas et al. (78) Details on colour of resistance band and, repetitions.
8	HOW: Replicate	Program illustrated with photographs, described in detail for each exercise level.
9	HOW: Home Program	Participants use any camera-equipped device for virtual group room access. (Tablet loans available from the hospital). Sessions hosted via Hospital-to-Citizen videoconference software (Region Zealand).
10	HOW: Nonexercise	None.
11	HOW: Adverse Events	Monitored via a daily patient diary and medical record reviews at 6-month follow-up.
12	WHERE: Location	Home-based.
13	WHEN, HOW MUCH: Dosage	60 minutes of resistance training with resistance bands twice weekly for 6 months. Details on sets, repetitions, duration, intensity. Progression model follows Dalgas et al. (78).
14	TAILORING: WHAT, HOW	Generic program with varying difficulty levels. Exercise diaries to record attendance, difficulty, sets, repetitions (78).
15	TAILORING: Decision Rule	Progression guided by established tools like OMNI scale (121)
16	Compliance: HOW WELL: Planned, Actual	The research group will test the intervention. The physiotherapist attends in another tele-rehabilitation session in order to deliver and supervise the PE program

The content is organized according to the Consensus on Exercise Reporting Template (CERT) (80) and the Template for Intervention Description and Replication (TIDieR) checklists (81), to ensure comprehensive, transparent, and reproducible reporting of the exercise and self-management intervention components.

### Interventions

2.7

Participants in the intervention group will initially in-person receive both verbal and written instructions on using the online platform and have a one-on-one virtual session with the physiotherapist to test the setup. Resistance bands will be provided post-randomization, and tablets will be available for loan if needed. The sessions will occur on a secure platform used by Region Zealand, tested and proven feasible in a mixed-methods study in patients with osteoarthritis and comorbidity (75).

The e-based exercise intervention is comprised of 6-months of supervised home-based resistance training for the lower extremities, conducted twice weekly **Figure 2**. The focus on the lower extremities is due to the pronounced impairment of lower extremity muscle strength compared to the upper extremities in pwMS (76). The intervention builds on two previous studies on supervised progressive resistance training for pwMS, which effectively improved walking performance (77, 78). The original protocol is modified to e-delivery (78), incorporating six exercises including, hip flexion, hip abduction, knee flexion and extension, ankle dorsal flexion, and gluteal bridge, using resistance bands **Figure 3**. Furthermore, resistance band training has been beneficial for the upper extremity in pwMS in home-based training programs (79) (**Figure 4**).

**Figure 2 f2:**
[figure not shown]
Level Progression per Patient. Each line (with circular markers) represents one of the 16 patients’ weekly progression through exercise levels 1–3 over a 12-week protocol. Vertical jitter has been applied to markers to prevent overlap, and each patient is assigned a distinct color. The x-axis shows Week 1–12; the y-axis shows Level (1 = easy, 3 = hard).

**Figure 3 f3:**
[figure not shown]
Band Progression per Patient. Each line (with circular markers) tracks one patient’s progression through theraband resistance bands (yellow→red→green→blue→black→gold) over the same 12 weeks. Vertical jitter separates overlapping points; colors match those in **Figure 1** for patient consistency. The x-axis shows Week 1–12, and the y-axis is labeled with band names in order of increasing resistance.

**Figure 4 f4:**
[figure not shown]
A comprehensive guide for a full-body warm-up and exercise routine aimed at enhancing joint mobility and muscle flexibility. The routine is segmented into six core exercises, each targeting specific areas of the body, supplemented by a warm-up sequence and a stretching sequence for overall muscle preparedness and recovery.

All 48 sessions will be conducted in virtual groups of 6–8 participants, supervised by an experienced physiotherapist, connected to the virtual group from an exercise facility at the hospital using a 65” widescreen with computer hardware. Participants will perform exercises with a fast concentric phase and a slow eccentric phase. The load will be adjusted using different resistance bands. The progression model for sets, repetitions, and load follows the approach used by Dalgas et al. (78), which specifies: week 1–4 with 3 sets of 10–12 repetitions at a load of 15 repetitions maximum (RM), week 5–8 with 3 sets of 12 repetitions at a load of 12 RM, week 9–12 with 4 sets of 12 repetitions at a load of 12 RM, week 13–16 with 4 sets of 10 repetitions at a load of 10 RM, week 17–20 with 4 sets of 8 repetitions at a load of 8 RM, and week 21–24 with 3 sets of 8 repetitions at a load of 8RM. The participant is allowed 2 to 3 minutes of rest between sets and exercises.

Usual care refers to routine MS physiotherapy provided once weekly in accordance with Danish clinical practice. All care received during the trial period, including any additional physiotherapy sessions, will be systematically recorded to ensure transparency and comparability across groups.

The details of the exercise therapy component, including activities, duration, frequency, and methodologies, are reported in accordance with the Consensus on Exercise Reporting Template (CERT) (80), ensuring clarity and replicability. For the self-management component, the intervention is described following the Template for Intervention Description and Replication (TIDieR) checklist (81). A comprehensive overview of both components is provided in 1.

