### Sample size calculation

2.17

A sample size calculation for the PE RCT was conducted to assess the effect of the intervention on the primary outcome, the 6-Minute Walk Test (6MWT), while accounting for comorbidity status and any potential interaction between comorbidity and the intervention. The calculation was based on:

A two-way factorial design incorporating intervention group (PE vs. control) and comorbidity status (yes/no) as binary factors, with a binary outcome based on the 6MWT, reflecting whether participants achieved a clinically meaningful improvement.A logistic regression model including intervention, comorbidity, and their interaction term as covariates.

The null hypothesis (H_0_) of no treatment effect was tested against the alternative hypothesis (H_1_) as either a main effect of the intervention or a significant intervention–comorbidity interaction, using a chi-square test derived from the logistic regression model.

Assumptions for the calculation were as follows: in the control group, it was assumed that 40% of participants with comorbidity and 20% without comorbidity would fail to achieve a clinically meaningful improvement in 6MWT. In contrast, in the intervention group, these proportions were expected to be reduced to 10% and 20%, respectively. This corresponds to a relative risk of 0.5, which is considered clinically significant.

Based on 10,000 simulation runs, a total of 73 participants per combination of intervention and comorbidity status (i.e., 292 participants in total) would be required to achieve approximately 80% statistical power at a 5% significance level. The simulations were performed using R software, version 4.1.2.

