### Statistical analysis

2.18

All data generated and collected during the project will undergo comprehensive statistical analysis using both traditional and advanced modeling techniques. The analyses will follow the intention-to-treat (ITT) principle as the primary analytic strategy. A per-protocol (PP) analysis will be conducted as a secondary approach, restricted to participants in the intervention group who meet the following criteria: (1) attendance of at least 75% of the prescribed exercise sessions, (2) completion of at least one follow-up assessment (e.g., at 6 months), and (3) submission of required self-report data such as exercise diaries and PROMs.

To evaluate the efficacy of the PE intervention, longitudinal changes in outcomes such as exercise capacity, functional abilities, and patient-reported measures will be analyzed using a multivariable regression model.

These models account for repeated measurements within individuals over time and are well suited to the handling of missing data under a missing-at-random assumption.

In parallel, changes in clinical disease biomarkers and standard clinical outcomes (e.g. EDSS, relapse rate) will also be examined using mixed-effects models for both within-group and between-group comparisons. Particular attention will be given to biomarkers that reflect MS activity or progression (e.g., serum GFAP, NfL), with adjustment for relevant covariates such as age, sex, and disease duration.

Key statistical analyses will include:

Association analyses, where logistic regression models will be used to assess the relationships between clinical outcomes and explanatory variables such as comorbidity status, age, and sex, including testing for potential interaction effects.Correlation analyses, where Pearson or Spearman correlation coefficients will be estimated to explore associations between multiple clinical endpoints, aiding in the interpretation of the multidimensional impact of MS.Predictive modeling of disease progression, which will be pursued as part of a follow-up analysis. We aim to construct models to predict MS progression by integrating disease biomarkers and vascular comorbidity risk factors. To this end, lasso logistic regression models will be employed, and model performance will be assessed using Area Under the Curve (AUC) metrics.

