#### Patients’ experiences with the feasibility study

2.20.2

By an individual conversation after exercise at the feasibility study the participants expressed their thoughts. They emphasized that the daily patient diary documentation for monitoring AE needed professional supervision. Participants experienced challenges incorporating digital exercise into their work-life routines. Observations further suggested that groups with having comparable age and PA levels tended to perform more cohesively. The positive experiences included the ease of logging in, the value of communication and the supervision performed by the physiotherapist. Moreover, a short structured post-exercise discussion with physiotherapist appeared to enhance social interaction and motivation.

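### The exercise arm trains in virtual groups of 6–8, but the sample size makes no allowance for correlation within groups, so the treatment-effect standard error may be too small

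*Protocol article*

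**What the plan says.** Allocation is individual: "Patients will be randomized in a 1:1 ratio into groups receiving either usual care or usual care plus a 6-month e-based PE program" (Section 2.6), with 150 patients planned per arm (Abstract). Delivery in the exercise arm is by group: "All 48 sessions will be conducted in virtual groups of 6–8 participants, supervised by an experienced physiotherapist" (Section 2.7; Table 1 gives the same group size). The Abstract describes sessions "supervised online by physiotherapists, two 60-minute sessions per week for 6 months", with physiotherapists in the plural. The comparator is described without any group format: "Usual care refers to routine MS physiotherapy provided once weekly in accordance with Danish clinical practice" (Section 2.7).

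The sample size in Section 2.17 comes from a simulation based on "A logistic regression model including intervention, comorbidity, and their interaction term as covariates". It arrives at 73 patients per cell, 292 in total, for about 80% power at the 5% level. No exercise group, ICC or design effect enters.

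On the analysis, Section 2.18 says of its efficacy models: "These models account for repeated measurements within individuals over time". Neither exercise group nor physiotherapist is named as a model term.

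Section 2.20.2 reports from the feasibility study that "groups with having comparable age and PA levels tended to perform more cohesively", and that a short discussion after exercise seemed to help social interaction and motivation.

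**The concern.** Patients who exercise together share peers, time slot and supervision. Their outcomes may therefore be more alike than those of patients in different groups. Here that sharing is introduced after randomisation and, as far as the text shows, in one arm only.

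If the correlation is positive and the analysis ignores it, the variance of the exercise-arm mean is underestimated. Confidence intervals are then too narrow and the test rejects a true null more often than 5%. If the analysis does account for it, the power in Section 2.17 is optimistic, because that figure was obtained without any such correlation.

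**Working it through.** **Inputs.** From the protocol: group size m = 6–8, 150 per arm, 73 per cell, and control failure rates of 40% (with comorbidity) and 20% (without). Assumed: ICC 0.01–0.10, clustering in the exercise arm only, and exercise-arm failure rates of 20% and 10%. That last assumption follows the stated relative risk of 0.5. Section 2.17 prints the two rates in the opposite order, which is a separate matter.

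**Number of groups.** 150/8 = 18.75 and 150/6 = 25, so about 19–25.

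**Reproducing the plan's figure.** Simulating independent patients (200,000 runs, 73 per cell, joint 2-df test of intervention and interaction) gives power of 80.6% (Wald), 81.6% (score) and 82.2% (likelihood ratio). The stated 292 thus reproduces with independent patients and carries no clustering allowance. Two approximations by noncentral chi-square, with noncentrality λ summed over the two comorbidity strata, bracket these values:
- Risk-difference scale: λ = 0.20²/[(0.24+0.16)/73] + 0.10²/[(0.16+0.09)/73] = 7.30 + 2.92 = 10.22; power 82.4%.
- Log-odds scale: λ = 0.981²/[(1/0.24+1/0.16)/73] + 0.811²/[(1/0.16+1/0.09)/73] = 6.74 + 2.77 = 9.51; power 79.4%.

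**Standard error and type I error, unadjusted 1-df test.** Design effect in the exercise arm: DE = 1 + (m−1)·ICC. True over naive SE of a 1:1 contrast with equal variances: r = √[(1+DE)/2]. Type I error: 2·[1−Φ(1.96/r)]. For m = 7:

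| ICC | DE | r | Type I error |
|---|---|---|---|
| 0.01 | 1.06 | 1.015 | 5.4% |
| 0.02 | 1.12 | 1.030 | 5.7% |
| 0.05 | 1.30 | 1.072 | 6.8% |
| 0.10 | 1.60 | 1.140 | 8.6% |

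Expressed against the true SE, the naive SE is short by 1 − 1/r: about 3%, 7% and 12% at ICC 0.02, 0.05 and 0.10.

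**Power of a cluster-corrected 2-df test at N = 292.** The exercise-arm variance is inflated by DE if groups form within a comorbidity stratum. If groups are mixed half and half, the factor is 1 + ICC·(m−1)/2, with a matching covariance between strata. Both cases are covered below, for m = 6–8:

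| ICC | Risk-difference scale (82.4% at ICC 0) | Log-odds scale (79.4% at ICC 0) |
|---|---|---|
| 0.02 | 80–81% | 76–77% |
| 0.05 | 77–79% | 71–73% |
| 0.10 | 72–75% | 63–68% |

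The lowest value (log-odds, m = 8, ICC 0.10, DE = 1.7, groups within stratum): λ = 0.981²/[(1/0.24+1.7/0.16)/73] + 0.811²/[(1/0.16+1.7/0.09)/73] = 4.75 + 1.91 = 6.66; power 63%.

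**Sensitivity to the printed rates.** With exercise-arm rates of 10% and 20% as printed, independent-patient power is 97.9% (Wald). In mixed groups at ICC 0.02–0.10, corrected power stays at about 98% on the risk-difference scale and about 90–94% on the log-odds scale. The loss below 80% therefore belongs to the relative-risk-0.5 reading, which is the one that reproduces 292.

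**The case against.** The strongest case on the other side has four parts.

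- **The ICC may be near zero.** Resistance is set per participant, the 6MWT is an individual test, assessors are blinded, and feasibility attendance of about 63% dilutes shared exposure. At ICC 0.01 the type I error is about 5.4%. This stands: only the upper part of the assumed range is material.
- **The article condenses the plan.** Random-effect structure is commonly left to an analysis plan, which is not shown, and Section 2.18 does not say its models handle repeated measurements and nothing else. This stands for the model detail. It does not reach Section 2.17, where the model and the resulting power are stated.
- **The feasibility remark is informal.** It concerns cohesion during sessions, not correlated change in 6MWT. It makes a group effect plausible but does not measure one.
- **One-arm clustering is inferred.** The format of usual-care physiotherapy is not described, so treating controls as independent is reasonable but undocumented.

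A reader might infer that patients stay in fixed groups under one physiotherapist. The text says neither. Group stability is not stated, and the wording on physiotherapists is singular in Section 2.7 and plural in the Abstract. If patients move between groups, the correlation may be weaker and differently structured. If one physiotherapist led every group, that influence would be confounded with arm rather than act as clustering.

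A reader might also infer that ignoring clustering takes power down to the low values above. It does not. On a generic 1-df test starting from 80%, the unadjusted test has power Φ[(2.80−1.96)/r], about 79%, 78% and 77% at ICC 0.02, 0.05 and 0.10 with 7 per group. Its problem is the inflated type I error. The larger power losses belong to the corrected analysis.

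**Conclusion.** The point holds conditionally. The exercise arm is delivered in groups, and the published power rests on independent patients. If the group ICC is positive, the unadjusted standard error is too small. How much depends on an ICC that the documents do not give: negligible to small at 0.01–0.02, material at 0.05–0.10. That the standard error will certainly be too small is not established.

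The sizes assume 6–8 per group, stable membership, independent controls and, for power, the relative-risk-0.5 reading of Section 2.17. Changing membership would alter the form of the model, not the need to consider it. This is a worthwhile, inexpensive improvement and not a flaw that undermines the trial.

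**What to change.** - **Section 2.7:** state whether a patient stays in the same exercise group for the whole programme and how physiotherapists are assigned to groups.
- **Data capture:** record exercise-group and physiotherapist identifiers per session in REDCap. Attendance is already recorded by the physiotherapist after each session. The identifiers are easiest to capture as groups form.
- **Section 2.18:** fit a partially nested mixed model with a random effect for exercise group in the intervention arm only, each control treated as a singleton, and small-sample degrees of freedom, given only about 19–25 groups. If patients change groups, use a multiple-membership version.
- **Section 2.17:** rerun the simulation with group delivery and report power over a stated ICC range. This needs no extra patients; the aim is an accurate power statement.

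The cost is two identifiers and one random-effect term. The downside is slightly wider confidence intervals and a slightly lower stated power.
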